## Abstract

**Background:**

The current standard operation for proximal gastric and gastroesophageal junction (P/GEJ) cancers with limited esophageal extension is total gastrectomy (TG). TG is associated with impaired appetite and weight loss due to the loss of gastric functions such as production of ghrelin and with anemia due to intrinsic factor loss and vitamin B_12_ malabsorption. Theoretically, proximal gastrectomy (PG) can mitigate these problems by preserving gastric function. However, PG with direct esophagogastric reconstruction is associated with severe postoperative reflux, delayed gastric emptying, and poor quality of life (QoL). Minimally invasive PG (MIPG) with antireflux techniques has been increasingly performed by experts but is technically demanding owing to its complexity. Moreover, the actual advantages of MIPG over minimally invasive TG (MITG) with regards to postoperative QoL are unknown. Our overall objective of this study is to determine the short-term QoL benefits of MIPG. Our central hypotheses are that MIPG is safe and that patients have improved appetite after MIPG with effective antireflux techniques, which leads to an overall QoL improvement when compared with MITG.

**Methods:**

Enrollment of a total of 60 patients in this prospective survey-collection study is expected. Procedures (MITG versus MIPG, antireflux techniques for MIPG [double-tract reconstruction versus the double-flap technique]) will be chosen based on surgeon and/or patient preference. Randomization is not considered feasible because patients often have strong preferences regarding MITG and MIPG. The primary outcome is appetite level (reported on a 0-10 scale) at 3 months after surgery. With an expected 30 patients per cohort (MITG versus MIPG), this study will have 80% power to detect a one-point difference in appetite level. Patient-reported outcomes will be longitudinally collected (including questions about appetite and reflux), and specific QoL items, body weight, body mass index and ghrelin, albumin, and hemoglobin levels will be compared.

**Discussion:**

Surgeons from the US, Japan, and South Korea formed this collaboration with the agreement that the surgical approach to P/GEJ cancers is an internationally important but controversial topic that requires immediate action. At the completion of the proposed research, our expected outcome is the establishment of the benefit and safety of MIPG.

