## Methods/design

This is a multicenter, open-label, prospective cohort study comparing outcomes of MIPG (trial procedure) and MITG (standard of care, control group). We expect to enroll a total of 60 patients in this study (30 per group). Patients will be recruited from and treated at MD Anderson Cancer Center, Mayo Clinic, Memorial Sloan Kettering Cancer Center, Yonsei University, and Keio University, after Institutional Review Board approval for each institution. We plan to enroll at least 20 patients each from Asian (Keio University and Yonsei University) and US (MD Anderson, and Mayo Clinic Minnesota, and Memorial Sloan Kettering Cancer Center) institutions. The total study duration is expected to be 60 months (including enrollment and follow-up). We will prospectively collect PROs longitudinally for a 1-year period. Other clinical factors will also be collected to investigate factors associated with improved PROs.

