### Statistical methods

The primary outcome is appetite level score (with 0 being the best and 10 being the worst) according to the MDASI-GI + (Question #8) at 3 months after surgery. We will enroll a total of 64 patients in order to have 60 evaluable patients at 3 months after surgery (i.e., assuming a 5% attrition rate). With 30 patients expected in each cohort, this study will have 80% power to detect a one-point difference in appetite level score using a two-sample *t*-test with a 5% significance level and assuming a common standard deviation of 1.35 (nQuery Advisor 7.0). We will also compare serum ghrelin levels at 3 months after surgery. For the primary analyses, we will apply the inverse probability treatment weights using propensity scores for assessing the difference between the two surgical groups. Inverse probability weighting is applied by weighting the outcome measures by the inverse of the probability of an individual with a given set of covariates being assigned to their treatment (i.e., propensity score). The propensity scores will be derived through fitting a multiple logistic regression model with MIPG (vs. MITG) as the outcome variable. Then, in the presence of measured confounders, we can estimate the difference between the two treatment groups via inverse probability weighting of the study subjects. For the regression analyses described below for assessing the “surgical procedure” effect, the inverse probability treatment weights using propensity scores will be applied as appropriate in addition to any standard statistical methods. The two-sample t-test or Wilcoxon rank-sum test will also be used to compare the appetite level or ghrelin level at 3 months, as well as the percent change from baseline, between the two cohorts. We will longitudinally collect PROs (using the fully translated MDASI-GI +) and compare specific items and overall scores as well as body weight, body mass index, and albumin and hemoglobin levels at 1, 3, 6, and 12 months after surgery in the cohorts. A linear mixed effects model will be fit to assess the change in QoL over time while accounting for potential intra-patient correlations. “Time” points will be included as a fixed effect, and “patient” will be included as a random effect. The surgical procedure received and use of adjuvant or neoadjuvant therapy will be included as covariates. Similar analyses will be performed to assess the changes in body weight, body mass index, and albumin and hemoglobin levels over time. The number of LNs examined pathologically, incidence of postoperative complications, operating room time, blood loss, and length of hospital stay will be compared. Continuous variables (such as length of hospital stay) will be assessed using the two-sample t-test or Wilcoxon rank-sum test. Categorical variables (such as type and severity of complications) will be assessed using Fisher’s exact test. Local–regional recurrence-free and overall survival will be estimated using the Kaplan–Meier method, and Cox regression analyses will be performed to assess the association with patient characteristics and surgical procedure received. The 3-year loco-regional recurrence rate will be estimated along with the 95% confidence interval. Missing data will be excluded from analysis and no missing data imputation will be performed. Sensitivity analyses to investigate factors associated with PRO scores, including but not limited to country (west vs. east), tumor location, types of reconstruction after PG, use of neoadjuvant and adjuvant therapy, use of jejunostomy or nutrition status, on PRO scores will be performed.

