This proposal is novel because it is the first international collaborative study as well as the first American study to prospectively investigate the benefits of MIPG with anti-reflux techniques. The research is culturally innovative because we will focus on PRO as the primary outcome, thus promoting a growing appreciation of the importance of patient-oriented care in the field of surgical oncology [24]. Theoretical benefits of PG, such as an improved hemoglobin level and reduced weight loss, become clinically significant only when QoL is improved, which can only be measured using PROs. The primary endpoint (appetite level) will be serologically validated with ghrelin level, which is an appetite-stimulating hormone that is known to decrease after TG [5]. Expected confounding factors that would affect postgastrectomy PROs, such as use of neoadjuvant therapy and different types of reconstruction after PG, will be carefully analyzed in sensitivity analyses. In addition, our study will determine the safety and feasibility of MIPG (including using a robotic approach) in the international setting. This transpacific collaboration between high-volume academic cancer centers will establish the foundation for future larger trials in the field of gastric cancer surgery.

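### The protocol article says the study will establish the safety of MIPG, but about 30 patients per group and an unweighted test of difference cannot support that conclusion

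*Protocol article*

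**What the plan says.** Safety appears as a hypothesis and as a promised result. The Abstract's Background says "Our central hypotheses are that MIPG is safe", and the Rationale section repeats this for PG. The Abstract's Discussion says "our expected outcome is the establishment of the benefit and safety of MIPG". The main Discussion says "our study will determine the safety and feasibility of MIPG (including using a robotic approach) in the international setting".

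The formal aims are more modest. Study objectives lists safety among matters to be investigated, after the appetite and patient-reported outcome aims. Safety measures lists 90-day complications, length of stay and 90-day readmission as items to be recorded.

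Statistical methods contains one sample-size calculation, for appetite: "We will enroll a total of 64 patients in order to have 60 evaluable patients at 3 months after surgery", and with 30 in each cohort "this study will have 80% power to detect a one-point difference in appetite level score". For safety it says "Categorical variables (such as type and severity of complications) will be assessed using" Fisher's exact test, and it gives continuous measures such as length of stay a t-test or Wilcoxon test. The inverse probability weights are assigned to the primary analyses and, as appropriate, to the regression analyses of the procedure effect.

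Under Details of surgery, the procedure follows patient choice and surgeon discretion. Patients converted to open laparotomy are dropped from the analyses and counted as screening failures, so that others can be enrolled in their place.

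**The concern.** A test of difference can reject equality. It cannot show that two procedures are equally safe or that one is acceptably safe. Here it would be applied to a sample chosen for a different endpoint, so its sensitivity to harm is whatever 30 per group happens to give.

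Two features weaken a safety conclusion further. Allocation is by preference, yet the Fisher comparison is not a regression and so, as written, is not weighted. And conversion to open surgery is itself relevant to safety; with those patients removed, the comparison describes only operations completed by the minimally invasive route.

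At stake is the statement that the study will hand on. The Rationale looks ahead to wide adoption of MIPG. A report that MIPG is safe could rest on data that are compatible with a large excess of complications.

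**Working it through.** **1. The plan's own figures.** Inputs from Statistical methods: difference 1 point, SD 1.35, 30 per group, 5% level (taken as two-sided). Noncentrality = 1 / (1.35 × √(2/30)) = 2.87 with 58 degrees of freedom, which gives power of 80.5% against the stated 80%. Enrolment: 60 / 0.95 = 63.2, rounded up to 64. Both figures reproduce. The appetite sample size is not in question.

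**2. Power of the complication comparison.** Inputs: 30 v 30 (Statistical methods), Fisher's exact test (same section), two-sided 5% (assumed, since no level is stated for this test). The article gives no expected 90-day complication rate, so the MITG rate is an assumption shown over a range. Exact power is the sum, over all pairs of event counts (i, j), of Bin(i; 30, p₁) × Bin(j; 30, p₂) for the pairs where the Fisher p-value is at most 0.05. Here p₂ = 2p₁.

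| Assumed MITG rate | MIPG rate if doubled | Power | Chance of a non-significant result |
|---|---|---|---|
| 5% | 10% | 2% | 98% |
| 10% | 20% | 10% | 90% |
| 14.3% | 28.6% | 18% | 82% |
| 20% | 40% | 30% | 70% |
| 28% | 56% | 50% | 50% |
| 30% | 60% | 56% | 44% |
| 35% | 70% | 71% | 29% |

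The 14.3% row is only an anchor. It is the late-complication rate after TG in the randomised trial described in the Discussion, not a 90-day rate.

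Counting all 64 enrolled patients (32 v 32) changes little: 11% power at 10%, 33% at 20% and 62% at 30%.

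**3. How large an excess would be needed.**
- From a 20% MITG rate, the MIPG rate would have to be about 58% for 80% power (exact value 81%).
- With 6/30 events on MITG, significance needs 15/30 on MIPG. With 3/30, it needs 11/30.

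**4. What equal results would leave open.**
- At observed rates of 20% in both groups, the half-width of the 95% interval is 1.96 × √(2 × 0.2 × 0.8 / 30) = 0.202, or about ±20 points.
- The Newcombe interval gives the same at 6/30 each, ±17 points at 3/30 each, and ±22 points at 9/30 each.
- For a type of complication not seen at all in 30 MIPG patients, the upper limit is 1 − 0.025^(1/30) = 11.6%.

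**5. Loco-regional recurrence.** Statistical methods already provides Kaplan–Meier estimation, Cox regression on surgical procedure (a regression, so weights may apply) and a 95% confidence interval for the 3-year rate. The reporting gap found for complications is not present here.

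**The case against.** The best defence is that the strong wording sits in the Abstract and Discussion, while the formal objectives only promise to investigate safety. The overall objective concerns quality of life, and the Discussion presents the study as groundwork for larger trials. A condensed article may also leave a margin or precision target for a secondary endpoint to the full protocol. All of that is fair, and it limits the point to the stated claim and the safety reporting. It does not withdraw the claim, because the article itself states the conclusion, the sample size and the test, and these do not fit together.

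Three stronger readings are tempting, and the document does not support them:

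- **That a doubling of complications would be missed whatever the base rate.** This depends on the MITG rate. Above about 28% a doubling would be detected more often than not. The article defines complications broadly, so a rate that high cannot be ruled out.
- **That 3-year recurrence has the same defect.** It does not, since an interval and Cox regression are already planned.
- **That the investigators will read non-significance as safety.** No passage says so. The article sets no such rule; it only leaves room for that reading.

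**Conclusion.** The concern holds in a limited form. The article says that the study will establish or determine the safety of MIPG. About 30 patients per preference-chosen group, compared for complications by an unweighted Fisher test with open conversions excluded, cannot support that statement at any base rate, because a test of difference does not demonstrate safety.

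The size of the weakness depends on an MITG complication rate that the article does not give. Power to detect a doubling runs from 2% at an assumed 5% to 56% at an assumed 30%, so a non-significant result is the likelier outcome for rates below about 28%. Equal observed rates of 20% would leave roughly ±20 points of uncertainty. These figures assume a 30:30 split and a two-sided 5% level.

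The fault lies in the conclusion promised and in how safety is reported, not in the primary sample size. It is worth correcting because it changes what the study may conclude.

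**What to change.** 1. In the Abstract and the Discussion, replace the promise to establish or determine safety with a statement that the study will estimate it. Reword the safety hypothesis in the Abstract's Background and the Rationale to match.
2. In Statistical methods, report 90-day complication and readmission rates by group, with the difference and its 95% confidence interval, using the same propensity weights as the primary analysis. Fisher's test may stay as a supplement.
3. State that a non-significant test will not be taken as evidence of safety.
4. In the safety summary, report conversions to open surgery, and the complications in those patients, by intended procedure. Leave the primary appetite population unchanged.
5. For 3-year loco-regional recurrence, keep the planned analysis and apply the same restraint to the conclusion.

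The cost is a more modest claim, a little more analysis, and safety follow-up of the converted patients. The sample size does not change.

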**Trial registration:**

This trial was registered with Clinical Trials Reporting Program Registration under the registration number NCI-2022–00267 on January 11, 2022, as well as with ClinicalTrials.gov under the registration number NCT05205343 on January 11, 2022.

## Background

The current standard surgical procedure used to treat proximal gastric and gastroesophageal junction (P/GEJ) cancers with limited esophageal extension is total gastrectomy (TG), unless the tumor is small (< 3 cm in diameter) and contained in the mucosal layer (pT1a); such tumors can be removed via endoscopic mucosal resection [1]. TG is associated with impaired appetite and weight loss [2–4] due to the loss of gastric functions such as production of ghrelin (the “hunger hormone” secreted by the stomach) [5] and with anemia due to intrinsic factor loss and vitamin B_12_ malabsorption. Theoretically, proximal gastrectomy (PG) can mitigate these problems by preserving gastric function. However, PG with direct esophagogastric reconstruction is associated with severe postoperative reflux and poor quality of life (QoL) and is therefore rarely performed in Western countries, including the United States [6, 7]. The lack of an effective surgical procedure that preserves gastric function and postoperative QoL for patients with P/GEJ cancers is a critical gap.

With the recent development of effective post-PG anti-reflux reconstruction techniques, such as double-tract reconstruction and the double-flap technique, PG has been increasingly used to treat proximal gastric cancer in South Korea and Japan [8–13]. Researchers in the KLASS-05 trial (NCT02892643) have recently reported results comparing outcomes at 2 years after PG with outcomes at 2 years after TG in patients with cT1N0 proximal gastric cancer, and these results showed that PG reduced the need for vitamin B_12_ supplementation and improved some QoL measurements. However, it remains unknown whether PG with double-tract reconstruction or the double-flap technique has short-term postoperative QoL advantages over TG [8, 12, 13]. In addition, the theoretical disadvantages of PG include incomplete lymph node (LN) removal, which may result in recurrence, and the potential for a second gastric cancer in the remnant stomach. Moreover, delayed gastric emptying of the remnant stomach can cause upper gastrointestinal symptoms such as reflux and bloating. The QoL benefits of PG must therefore be clearly demonstrated before encouraging its use in Western countries.

PG is commonly indicated for cT1 proximal gastric cancer in South Korea and Japan [8–13], with reported excellent overall and recurrence-free survival. Given the low incidence of LN metastasis in cT1 gastric cancers, PG is considered safe for cT1 proximal gastric cancer. A recent Japanese prospective study of GEJ adenocarcinoma reported a low incidence of LN metastasis at peripyloric stations (suprapyloric [station 5] and infrapyloric [station 6]) regardless of tumor stage [14], and surgeons thus began performing PG for GEJ cancers in Eastern Asia. As a result, Japanese Gastric Cancer Treatment Guidelines now recommend PG as a surgical option for GEJ cancers with limited esophageal extension [15]. In Western countries, although TG is considered the standard surgical procedure for P/GEJ cancers, Ivor Lewis esophagectomy, which uses the gastric conduit for reconstruction [16], is also commonly performed for GEJ cancers, suggesting that PG may also be oncologically safe for GEJ cancers. However, internationally and nationally, controversy remains as to whether and when PG is oncologically safe for GEJ cancers and whether PG provides better QoL than TG [6, 7]. An international collaboration is warranted to determine the benefits and safety of PG for P/GEJ cancers and thus standardize surgical care for patients with these cancers.

### Rationale

Surgeons at The University of Texas MD Anderson Cancer Center in Houston, Texas; the Mayo Clinic in Rochester, Minnesota; Memorial Sloan Kettering Cancer Center, New York; Yonsei University in Seoul, South Korea; and Keio University in Tokyo, Japan formed a collaboration to address the issue of the surgical approach for P/GEJ cancers, an internationally important but controversial topic that requires immediate action. Our central hypotheses are that PG is safe and that patients have improved levels of appetite after minimally invasive PG (MIPG) with effective anti-reflux techniques because of maintained secretion of ghrelin from the gastric remnant, which leads to better overall QoL compared with minimally invasive TG (MITG). The rationale for this project is that MIPG’s theoretical benefit of preserving gastric function, which can only be measured using patient-reported outcomes (PROs), must be demonstrated before widespread implementation of MIPG.

### Study objectives

The primary objective is to compare the short-term appetite of patients who undergo MIPG for gastric and gastroesophageal adenocarcinoma with that of patients who undergo MITG. We hypothesize that MIPG is associated with higher postoperative appetite levels compared with MITG, which would result in better nutritional status and less body weight loss after surgery.

The secondary objective is to assess PROs and nutrition measures and compare them between the MIPG and MITG groups. We will use the MD Anderson Symptom Inventory Gastrointestinal Cancer Module (MDASI-GI) questionnaire, along with an additional three experimental question items (MDASI-GI +), to collect preoperative and postoperative PRO measures of QoL, and we will check fasting ghrelin levels to correlate them with reported appetite levels. We will also investigate factors associated with improved QoL after surgery, safety of MIPG and MITG, and oncologic outcomes after MIPG and MITG.

## Methods/design

This is a multicenter, open-label, prospective cohort study comparing outcomes of MIPG (trial procedure) and MITG (standard of care, control group). We expect to enroll a total of 60 patients in this study (30 per group). Patients will be recruited from and treated at MD Anderson Cancer Center, Mayo Clinic, Memorial Sloan Kettering Cancer Center, Yonsei University, and Keio University, after Institutional Review Board approval for each institution. We plan to enroll at least 20 patients each from Asian (Keio University and Yonsei University) and US (MD Anderson, and Mayo Clinic Minnesota, and Memorial Sloan Kettering Cancer Center) institutions. The total study duration is expected to be 60 months (including enrollment and follow-up). We will prospectively collect PROs longitudinally for a 1-year period. Other clinical factors will also be collected to investigate factors associated with improved PROs.

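### Two sections set enrolment at 60 and the statistical section sets it at 64; stopping at 60 would leave 57 evaluable and about 78% power instead of the stated 80%

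*Protocol article*

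**What the plan says.** Three places give a total, and a fourth depends on it.

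- **Abstract, Methods:** "Enrollment of a total of 60 patients in this prospective survey-collection study is expected". The power statement that follows refers to 30 patients per cohort.
- **Methods/design:** "We expect to enroll a total of 60 patients in this study (30 per group"). The same paragraph asks for at least 20 patients each from the Asian and the US institutions.
- **Statistical methods:** "We will enroll a total of 64 patients in order to have 60 evaluable patients at 3 months after surgery", with the reason given as "assuming a 5% attrition rate". On power it states: "With 30 patients expected in each cohort, this study will have 80% power to detect a one-point difference in appetite level score". The inputs behind that figure are a t-test for two groups, a level of 5%, and an SD of 1.35 in both groups.
- **Details of surgery:** patients converted to open surgery, or found at surgery to have metastatic disease, leave the analysis and count as screening failures, so that others can be enrolled up to the accrual target. No number is attached to that target.

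**The concern.** The abstract and the design section attach enrolment to 60. The statistical section attaches enrolment to 64 and makes 60 the number evaluable at 3 months. Both figures cannot be the point at which accrual stops.

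The difference of four patients is the whole allowance for attrition. The replacement rule in Details of surgery covers open conversions and metastatic disease only. It does not cover a patient who has the planned operation and then gives no 3-month appetite score. Statistical methods excludes missing data without imputation, so each such patient reduces the primary analysis set. If 60 were taken as the accrual target, nothing in the plan would make up those losses. Recruitment runs at five institutions in three countries, so the figure should read the same wherever a site looks.

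**Working it through.** **Inputs, all from Statistical methods unless noted**
- Difference: 1 point on the 0–10 item. SD: 1.35.
- Significance level: 5%. The sidedness is not stated; two-sided is assumed here because it reproduces the plan's sample size (a one-sided test would need only 23.2 per group).
- Evaluable: 30 per group, 60 in all. Attrition: 5%. Enrolled: 64.
- Enrolled according to the abstract and Methods/design: 60.

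**Step 1. Reproduce the plan's power**

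Standardised difference d = 1/1.35 = 0.741. Noncentrality = d × √(n₁n₂/(n₁+n₂)).

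For 30 and 30: 0.741 × √(900/60) = 0.741 × 3.873 = 2.87, on 58 degrees of freedom. The noncentral t gives power of 80.5%. Solving for 80% gives 29.6 per group, hence 30. The stated 80% reproduces.

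**Step 2. Reproduce the inflation for attrition**

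60/(1 − 0.05) = 63.2, rounded up to 64. Check: 64 × 0.95 = 60.8 evaluable. The stated 64 reproduces.

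**Step 3. Apply the same attrition to 60 enrolled**

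60 × 0.95 = 57 evaluable, at best 29 and 28.

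Noncentrality: 0.741 × √(29 × 28/57) = 0.741 × 3.774 = 2.80, on 55 degrees of freedom. Power is 78.4%.

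**Step 4. Compare**

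| Enrolled | Evaluable at 5% attrition | Split used | Power, noncentral t | Power, normal approximation |
|---|---|---|---|---|
| 64 | 60.8 | 30 / 30 | 80.5% | 81.8% |
| 60 | 57 | 29 / 28 | 78.4% | 79.8% |

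Against the stated 80%, the shortfall is 80 − 78.4 = 1.6 points. Against the 80.5% actually attained at 30 per group, it is 80.5 − 78.4 = 2.1 points. The normal approximation puts it at 80 − 79.8 = 0.2 points, but the plan names a t-test, so the noncentral t figure is the matching one.

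**Step 5. Sensitivity to rounding of the SD**

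With SD from 1.345 to 1.354, power at 29 and 28 runs from 78.7% to 78.2%, and at 30 and 30 from 80.8% to 80.3%. Rounding does not change the picture.

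**Step 6. Does other text settle which total applies?**

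The regional minimum does not: 20 + 20 = 40 fits under either total. The replacement rule does not either, because its target has no number.

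**The case against.** The strongest reply is that the statistical section already explains how the two numbers relate: 64 go in so that 60 come out. The 60 in the design section carries the same split of 30 per group that the statistical section uses for its power, so it is most naturally the analysis target loosely described as enrolment. The abstract and design section also speak of expectation, whereas the section that derives the sample size speaks of intention. A reader who reaches that section can work out what was meant.

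Much of this stands. Nothing is miscalculated, and 64 is very probably the intended figure. But the article prints both totals as numbers enrolled, and the one operative rule that uses the total does not say which it means. The reader has to infer the answer.

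A second reply is that the loss of power is too small to matter. This also largely stands. A 1.6-point shortfall is modest, and it depends on an assumed SD. A reader might infer from the two totals that the trial is underpowered or its sample size wrongly derived. The documents do not support that, because the calculation in Statistical methods is sound at 64 enrolled. Nor do they show that any site would close accrual on the design section's figure; that consequence is conditional.

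**Conclusion.** The point holds as an inconsistency in the enrolment target, wrong as written: 60 enrolled in the abstract and Methods/design, 64 enrolled in Statistical methods, and an accrual target in Details of surgery that is tied to neither.

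Its size is four enrolled patients. If accrual stopped at 60 and attrition were 5%, 57 would be evaluable and power would be about 78% instead of the stated 80%.

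These power figures assume a two-sided 5% test, SD 1.35, a near-equal split and an unweighted comparison. The planned primary analysis is weighted by propensity score, and the split is only expected because patient and surgeon choose the procedure. Actual power may therefore differ from both figures, and the calculation above does not measure that.

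A reader might also infer that each procedure cohort should close at 32. The documents give no basis for this. They set no limit per procedure, and a limit would turn away eligible patients because of the operation chosen. That would be a new design rule, beyond what is needed to correct the total.

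**What to change.** - **Abstract (Methods) and Methods/design:** replace the enrolment of 60 with: 64 patients enrolled to give 60 evaluable (about 30 per procedure) at 3 months.
- **Details of surgery:** state that the accrual target is 64.
- **Statistical methods:** no change to the sample size calculation.
- Do not add a cap per procedure cohort.

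The cost is wording only, since 64 is already the figure in the section that derives the sample size. The correction is worth making before accrual closes, because the attrition allowance is hard to recover afterwards.
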